#### Inertial Data Labeling

The researchers will attend a supervised physiotherapy session for each patient once every 2 weeks to record exercise type and technique labels synchronously with inertial data collection, based on the input from the treating physiotherapist. The technique will be labeled as a binary variable, indicating if the treating physiotherapist was satisfied that the exercise was performed correctly (as intended). The treating physiotherapist will also make a record of prescribed home exercises and exercise type and technique evaluations at each supervised physiotherapy session.

#### Supervised Physiotherapy Video Recording

Color video recordings of supervised physiotherapy sessions will be made during 30 supervised inertial data collections. The videos will be used for the reliability analysis of the exercise type and technique labels assigned by the treating physiotherapist, and 2 blinded physiotherapists will review and reclassify the video data independently.

#### Home Physiotherapy Adherence Diaries

Patients will log their home physiotherapy activities in an adherence diary for 2 weeks, during the strengthening phase of their rehabilitation. Validation of the SPARS adherence measurement will include a comparison with these data.

#### Clinical and Return to Work Outcomes Data

Validated clinical outcomes will be collected to measure the relationship between home physiotherapy adherence and patient recovery. The following validated clinical outcome measures will be collected (1) pretreatment; (2) monthly through treatment; and (3) at 12-months final follow-up (items 1-3 only); these items are routinely collected by the Sunnybrook’s Working Conditions Program (WCP):

Work status (full-time, part-time, off-work, modified, or regular duties)Numeric Pain Rating Scale (NPRS)Disabilities of the Arm, Shoulder, and Hand (DASH) scoresRotator cuff strength testing using manual muscle testingShoulder active range of motion measured with a goniometer.

The NPRS is valid and reliable for clinical practice [94,95]. The DASH has proven reliability, validity, and responsiveness in patients with shoulder problems [96-98]. Manual muscle testing and range of motion measurement using a goniometer are standard accepted methods for rotator cuff strength testing and shoulder range motion evaluation in the clinical setting [99], with established validity and reliability [100-104].

#### Barriers to Adherence

The following potentially significant adherence predictors [12,105-110] will be collected for each patient at recruitment: age, sex, body mass index, dominant side involvement, symptom duration, mechanism of injury (traumatic or degenerative), rotator cuff tear thickness and size, type of operative procedures, comorbidity (cumulative illness rating scale [111]), smoking status, alcohol intake, opioid intake, cannabinoid intake, the baseline level of physical activity, education, marital status, job demands, socioeconomic status (current income), perceived social support (Enhancing Recovery in Coronary Heart Disease Social Support Inventory [112]), patient self-efficacy (2-item Pain Self-Efficacy Questionnaire [113]), Patient Expectation Questionnaire [114], and Hospital Anxiety and Depression Scale [115].

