### Adherence to Rotator Cuff Rehabilitation

Several studies on patients with rotator cuff pathology have measured rehabilitation adherence variables, including clinic attendance, adherence to postoperative restrictions, and home physiotherapy participation during rotator cuff rehabilitation [4,10,13,26,49-51]. Nonadherence (eg, to protective device use and clinic attendance) is more prevalent in workers’ compensation patients (52%) than nonworkers (4%) [10]. There is also a relationship between adherence and improved clinical outcomes in the nonoperative [50] and operative management [10,51] of rotator cuff pathology.

Unfortunately, adherence to home rotator cuff exercises has only been measured with adherence diaries [4,26,50] or in response to directed questioning [51]. The completion rates for the adherence diaries varied from 60% to 75% [4,26,50]. Furthermore, the validity of a patient’s self-reported adherence is questionable as a research instrument [52]. Therefore, the rate and effect of adherence to home rotator cuff exercise participation and technique remain unknown. The proposed study will address this knowledge gap in a cohort of 120 patients with rotator cuff pathology.

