### Factors Affecting Adherence

The barriers to adherence to supervised outpatient physiotherapy clinics have been summarized in a systematic review by Jack et al [12] in 2010. There was strong evidence to suggest that low baseline levels of physical activity; low in-treatment adherence to exercise; low self-efficacy, depression, and anxiety; helplessness; poor social support; greater perceived number of barriers to exercise; and increased pain during exercise are all significant barriers to physiotherapy adherence. The majority of studies reviewed measured adherence only in terms of clinic appointments. Several studies [60-64] investigated the barriers to adherence to unsupervised home exercise programs. However, these studies suffered from the limitations of the existing adherence diary instrument outlined previously (poor objectivity, poor compliance with the diary, and inability to measure technique adherence). The barriers to unsupervised home physiotherapy, therefore, remain uncertain; they will be explored in the proposed study.

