#### Aim 2: Measure the Rate of Adherence to Home Shoulder Physiotherapy, the Relationship Between Adherence and Recovery, and Identify Barriers to Home Physiotherapy Adherence

##### Objectives

The related objectives are as follows:

Inertial sensor data are collected during home physiotherapy for 120 patients with rotator cuff pathology over full treatment duration (up to 5 months).Technical failures preventing home data collection are less than 5%.Clinical outcomes: return to work status, shoulder range of motion, rotator cuff strength, and patient-reported outcomes of pain and disability are collected pretreatment, monthly through treatment (up to 5 months), and at 12-months final follow-up. The final follow-up exceeds 85%.A total of 23 potentially significant predictors of home physiotherapy adherence (identified in Methods: Barriers to Adherence) are collected for all study participants at the time of recruitment.

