### Recruitment

Patient recruitment began in July 2019. As of December 2019, 71 patients were screened for enrollment, of whom 65 patients met the inclusion and exclusion criteria. Of these, 46 patients consented and 19 declined to participate in the study. Of those recruited, 9 have worker’s compensation claims and 37 do not. Figure 2 shows the recruitment status and patient flow of the ongoing study.

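### The closed list of 23 adherence predictors leaves out workers' compensation status, which the plan links to poor adherence and already records, so the barriers analysis as specified would not test it

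*Protocol article*

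**What the plan says.** The Aim 2 objectives give a fixed count and say where the list is: "A total of 23 potentially significant predictors of home physiotherapy adherence (identified in Methods: Barriers to Adherence) are collected". Barriers to Adherence then names the variables that "will be collected for each patient at recruitment: age, sex, body mass index, dominant side involvement, symptom duration, mechanism of injury" and continues through tear characteristics, comorbidity, substance use and activity to the psychosocial scales. The work-related and socioeconomic stretch reads "education, marital status, job demands, socioeconomic status (current income), perceived social support". Compensation status does not appear, and neither does a pain score.

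Univariable and Multivariable Analyses takes adherence as the dependent variable. It tests each baseline adherence predictor, together with environment (home or clinic), and builds a multivariable model from the statistically significant ones, up to 12.

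Elsewhere the protocol gives compensation status some weight:

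- The Introduction's Overview names worker populations as a group in which adherence is particularly poor.
- Adherence to Rotator Cuff Rehabilitation says that nonadherence "is more prevalent in workers’ compensation patients (52%) than nonworkers (4"%), with protective device use and clinic attendance as its examples.
- Recruitment reports that 9 of those recruited have "compensation claims and 37 do not".
- Criterion Validity uses worker or patient subgroup as a moderator, and Algorithmic Fairness uses workers' compensation status as a subgroup.

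On pain, Factors Affecting Adherence ends its list of strong-evidence barriers with "increased pain during exercise are all significant barriers to physiotherapy adherence".

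**The concern.** Aim 2 sets out to identify barriers to home physiotherapy adherence. The one patient factor for which the protocol quotes group percentages is missing from the variables to be tested as barriers. The protocol gives no reason for this, and the variable is already in the study data.

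Two things follow if the analysis is run as written. First, a difference in home adherence between claimants and others would not be looked for in the analysis meant to find such differences. Second, listed predictors that travel with claim status (job demands and income are the obvious candidates) could pick up part of its effect and be reported as barriers themselves. That would reach beyond the paper: the ethics section foresees that patient profiles could steer resources or behavioural programmes, and Aim 3 builds an adherence-driven programme.

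**Working it through.** **1. Does the list close at the stated count?** Counting the comma-separated entries in Barriers to Adherence:

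- age, sex, body mass index, dominant side, symptom duration, mechanism of injury (6)
- tear thickness and size, operative procedure, comorbidity (9)
- smoking, alcohol, opioids, cannabinoids (13)
- physical activity, education, marital status, job demands, income (18)
- social support, self-efficacy, expectation, anxiety and depression scale (22)

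That is 22 entries. Counting tear thickness and tear size as two variables gives 22 + 1 = 23, the stated figure. The count is reproduced, and it leaves no place for an unlisted compensation variable.

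**2. Can compensation status enter the barriers model by another route?** The analysis section takes the baseline adherence predictors and adds environment only. The multivariable model draws on the significant members of that set. No other route is described.

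**3. Does another analysis fill the gap?**

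| Section | Role of worker or compensation status | Tests whether it predicts adherence? |
|---|---|---|
| Criterion Validity | Moderator; adherence explains change in clinical outcome | No, adherence is on the explanatory side |
| Algorithmic Fairness | Subgroup for classifier error rates | No, it concerns the classifier |
| Univariable and Multivariable Analyses | Not named | This is where the test would belong |

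Job demands and income are neighbouring variables, not claim status. Work status (full-time, off-work and so on) is collected as an outcome.

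**4. Is the variable in hand?** Recruitment gives 9 with claims and 37 without; 9 + 37 = 46, so every recruit is classified. The share with claims is 9/46 = 19.6%.

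**5. What could a test of it detect?** Assume that the share holds at the full sample and that each patient contributes one adherence value. Then 120 × 9/46 = 23.5, taken as 23 claimants against 97 others. For a two-sided 5% two-sample test with 80% power (normal approximation), the smallest detectable difference in standard deviations is

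(1.960 + 0.842) × √(1/n₁ + 1/n₂).

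| Assumed share | n₁ / n₂ | Detectable difference |
|---|---|---|
| 10% | 12 / 108 | 2.802 × 0.304 = 0.85 SD |
| 19.6% (9/46) | 23 / 97 | 2.802 × 0.232 = 0.65 SD |
| 50% | 60 / 60 | 2.802 × 0.183 = 0.51 SD |

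The test could find a fairly large difference and would be weak for a small one. Whether such a difference exists cannot be told from the documents.

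**6. Pain.** The cited barrier is pain during exercise. The nearest listed item is a two-item pain self-efficacy questionnaire, which does not measure pain level. The Numeric Pain Rating Scale is collected pretreatment and monthly as an outcome, and is not described as pain during exercise. The pretreatment score is therefore available, but only as a proxy.

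**The case against.** **A condensed article may leave covariates to a fuller document.** This would answer a list given as examples. Here the article states a total and a list that meets it, so the omission is in what the article itself fixes. Even so, no sentence promises compensation status as a barrier predictor. This is a gap between rationale and analysis, not a contradiction.

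**The analysis is exploratory, and the displacement of effects is not demonstrated.** This stands in part. The documents give no correlation between claim status and job demands, income or any other listed predictor, so misattribution is a possibility only. If claim status acts through job demands or anxiety, adjusting for it could also hide a modifiable barrier. That argues against forcing it into the model and for showing results with and without it.

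**Stronger readings that a reader might infer, and that the documents do not support:**

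- *The study cannot detect or adjust for compensation status.* The data are in hand, and worker or compensation status is used in two other analyses. The gap is confined to the barriers model as specified.
- *Baseline pain is a cited barrier that was left out.* The text cites pain during exercise; baseline pain is nowhere named as a barrier.
- *The omitted effect is known to be large.* With a 20% share, 52% against 4% gives overall nonadherence of 0.2 × 0.52 + 0.8 × 0.04 = 0.136 and a phi coefficient of 0.48 × 0.4 / √(0.136 × 0.864) = 0.56. At half the difference (28% against 4%) it is 0.24 × 0.4 / √(0.088 × 0.912) = 0.34. Neither figure sizes this point. The cited contrast is binary and illustrated by device use and clinic attendance, whereas participation here is a percentage of prescribed home exercise, whose rate the protocol says is unknown. Nor is the sample-size benchmark of R = 0.25 a comparator, since it concerns adherence against clinical outcomes.

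**Conclusion.** The point holds in limited form. The list of 23 is closed, it omits workers' compensation status, and the barriers analysis adds nothing but environment. The plan's own Introduction gives reason to test this variable, the study already records it, and the moderator analysis does not substitute for the test because it asks a different question.

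The size of any effect on home-exercise adherence, and of any misattribution to listed predictors, is unknown from the documents. The detectable difference of about 0.65 SD rests on the December 2019 claim share holding at 120 patients and on one adherence value per patient; it describes what a test could find, not what is there. The pain element is secondary: no pain measure is listed, and the available one is a proxy for the barrier cited.

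**What to change.** Add workers' compensation status (yes/no) to the candidates in Barriers to Adherence. Test it in the univariable analysis, and let it enter the multivariable model under the same rule as the others (statistically significant, maximum 12), or report a sensitivity model that includes it. Pretreatment Numeric Pain Rating Scale score can be added as a further candidate, described as a proxy for pain during exercise. If either is left out on purpose, say why.

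The stated count becomes 23 + 1 = 24, or 25 with the pain score. No new data are needed and the cap of 12 is unchanged. The cost is one or two extra univariable tests and, if selected, one or two of the 12 places. Making the change before the adherence results are seen avoids a post hoc addition.

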#### Data Management, Monitoring, and Reporting

The data for this project consist of the following (1) inertial sensor data; (2) video data; (3) clinical outcome scores; (4) adherence predictor variables; and (5) adherence diaries. Items 2-4 include personal information. Video data will be anonymized with face deidentification and audio removal. Data items will be linked with a subject identification number and stored on secure servers at Sunnybrook Research Institute, behind institutional firewalls, with restricted physical access. The database will be encrypted, and access will be limited to researchers carrying out activities related to the proposed study. Continuous data redundancy and versioning will mitigate the risk of large data loss.

When a patient attends supervised physiotherapy at the Holland Centre, their smart watch inertial data are uploaded to Google Cloud Storage. The retrieved data are immediately verified by a software tool that checks and reports the proper functioning of the sensors and correct watch usage to the researchers, ensuring that anomalies are detected promptly. Our research engineer will administer the study database, review the incoming data, and update the research team during monthly project meetings.

#### Smart Physiotherapy Activity Recognition System-Home Physiotherapy Participation Adherence

The ML algorithms underlying SPARS will be trained in a supervised learning framework to classify (recognize) different activities from the characteristic time series of inertial signals they produce in the smart watch inertial sensors. A detailed description of our implementation and its evaluation are presented in our previous pilot study [15] and our open-source software package for ML time series (seglearn) [116]. Briefly, sensor data are segmented into fixed-length windows (2-4 sec in length) that are learned by a deep convolutional recurrent neural network (CRNN) classifier. Once trained, the classifier can be used to reconstruct a record of activities from the recorded inertial sensor data.

The ML algorithms underlying SPARS will be trained and validated using the labeled inertial sensor data collected during supervised physiotherapy sessions. The trained SPARS algorithms will then generate a record of exercises performed from inertial sensor data collected during unsupervised home sessions and supervised sessions during which synchronous data labeling was not performed. Comparing the quantity and frequency of home exercises measured by SPARS with the prescribed exercises will serve as our measure of participation adherence. Participation adherence will be measured as a percentage of the prescribed activity over each 2-week interval of treatment.

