#### Inertial Data Collection

Each study subject will be provided with a smart watch to be worn on their affected extremity when performing the prescribed physiotherapy exercise. The smart watch must be worn for all physiotherapy exercise sessions conducted over the duration of treatment, up to a maximum of 5 months. This includes all supervised physiotherapy sessions at the Holland Centre and any physiotherapy exercise sessions conducted by the patient independently (home exercises). No alteration to the prescribed physiotherapy will be undertaken during this clinical validation study.

The smart watches purchased for this study will have a 9-axis IMU (3-axis accelerometer, 3-axis gyroscope, and 3-axis magnetometer). The inertial sensors will be sampled at 50 Hz and recorded to the internal memory storage on the smart watch. The inertial data will be encrypted using the Rivest–Shamir–Adleman public-key cryptosystem. The smart watch will permit up to 150 hours of sensor data recording to its 4 GB internal memory. The sensor data will be retrieved and removed from the smart watch when the patient attends supervised physiotherapy at the Holland Centre (2 times per week).

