A smart watch was selected as the platform for physiotherapy adherence tracking chiefly for patient comfort during exercise and ease of use. A significant proportion of the rotator cuff pathology demographic is elderly [16,17] and many have low technology literacy. The smart watch platform we have developed only requires that a patient put on their watch before physiotherapy exercise and that they ensure it is charged before doing so. This is in contrast to other systems that either require multiple sensors to be strapped to various points on the body [70] or a computer vision approach that requires some setup in the exercise environment to obtain and maintain an appropriate field of view [65]. In our setup, raw inertial data are processed using a modern deep learning approach, which we have shown previously to significantly outperform classical algorithms utilizing an engineered feature representation [15]. Although the deep learning approach requires significantly more computing resources for training, the inference time is comparable with classical models and feasible for evaluation either as a cloud service or directly on a patient’s mobile device [15].

There are a number of limitations to the proposed study. In the validation phase of this research, the act of measuring physiotherapy adherence may impact patients’ likelihood of adherence, even in a double-blinded noninterventional fashion, as proposed. Therefore, the assessed adherence rate in the study population may not be generalizable to populations that receive no tracking at all. A further limitation is that the ML algorithms validated in the clinic context will generalize well to the home setting. This risk will be mitigated by assessing algorithm generalization across multiple clinic sessions and to new patients (subject stratification). We assume that if that algorithm generalizes in both these cases, generalization to the home setting is also likely. As we also assess the criterion validity for adherence tracking, a positive relationship between adherence and recovery, if detected, it would serve as further evidence for the validity of algorithm construct.

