Despite the efforts we have invested in developing a simple, accurate, and robust method for tracking shoulder physiotherapy, tracking errors will inevitably occur and result in imperfect adherence measurement. These errors could be secondary to software glitches, poor algorithm generalization, accidental or intentional misuse or disuse, hardware failure, and others. Therefore, the adherence estimates that we calculate for each patient will be subject to these errors, which may be random or biased to certain study subjects. To mitigate and assess these effects, we will collect survey data from each patient on their use of the smart watches and ask each patient to manually complete a 2-week adherence diary so that we can compare the measured adherence with patient self-report.

A limitation of the final interventional phase of this study is the pilot sample size (N=20) and the absence of a true control group. Although we can compare the interventional cohort with historical controls in the validation cohort, a better comparison would be with a control group with no tracking at all as per the current standard of care. Ultimately, a larger randomized controlled trial (RCT) would be required to adequately assess the effect of an adherence-driven rehabilitation program on recovery. The pilot study we conduct is primarily powered to detect implementation challenges, refine the system design, and estimate the effect size as required preliminaries to funding and carrying out a larger multicenter RCT.

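### Participation adherence is SPARS-recorded exercise over all prescribed exercise, so home exercise lost to device failure or done without the watch counts as not done

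*Protocol article*

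**What the plan says.** **The definition.** Under Methods, SPARS-Home Physiotherapy Participation Adherence, the protocol article states: "Comparing the quantity and frequency of home exercises measured by SPARS with the prescribed exercises will serve as our measure of participation adherence". The next sentence sets scale and window: "Participation adherence will be measured as a percentage of the prescribed activity over each 2-week interval of treatment". Neither sentence contains a term for time worn or time validly recorded.

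**Wear.** Inertial Data Collection puts the duty on the patient: "The smart watch must be worn for all physiotherapy exercise sessions conducted over the duration of treatment, up to a maximum of 5 months".

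**Use of the measure.** Adherence is the explanatory variable for change in clinical outcomes (Criterion Validity). It is the dependent variable in the analysis of baseline predictors (Univariable and Multivariable Analyses). Age and education are among those predictors (Barriers to Adherence).

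**Safeguards.**
- Data Management, Monitoring, and Reporting: "The retrieved data are immediately verified by a software tool that checks and reports the proper functioning of the sensors and correct watch usage", with results going to the researchers.
- Aim 2, Objectives: "Technical failures preventing home data collection are less than 5" (per cent). This is a target for technical failure; none is set for non-wear.
- Concurrent Validity: SPARS counts are compared with the patient diaries by paired *t* test, Bland-Altman plots and ICC(2,1). The diary runs for 2 weeks.
- Discussion, Principal Findings: a survey of watch use is added.

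**The admission.** The same Discussion section lists among the expected sources of error "accidental or intentional misuse or disuse, hardware failure, and others", and accepts that they may affect some patients more than others. It also says of this patient population that "many have low technology literacy".

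**The concern.** The definition makes no distinction between an exercise that was not done and one that was not recorded. All of Aim 2 rests on this variable: the rate of home adherence, its relation to recovery, and the barriers to it.

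- **Rate.** Any recording loss pushes it downward.
- **Barriers.** If loss is related to a candidate predictor, difficulty with the watch can look like a barrier to exercise. The article supplies a possible route, since it describes the population as often elderly with limited technology skills and also tests age and education as predictors.
- **Recovery.** Loss that varies between patients adds noise to the explanatory variable and weakens the correlation on which the sample size was based.

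The article states a specific ratio. Followed as written, that ratio also applies to periods that the study's own verification tool has identified as faulty.

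**Working it through.** **1. The plan's own figure.** Sample Size gives N = 120, R = 0.25, 5% alpha and 80% power. Taking the test as two-sided (the article does not say), the noncentral *t* calculation gives 80.1%. Fisher *z* gives Φ(atanh(0.25) × √117 − 1.96) = 78.9%. The stated power reproduces and is not in dispute.

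**2. Effect on the rate.** Let *m* be the share of performed exercise that is not recorded. Then

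measured adherence = true adherence × (1 − *m*).

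The article gives no value for *m*, so these are assumptions:

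| True adherence | *m* = 5% | *m* = 10% | *m* = 20% |
|---|---|---|---|
| 50% | 47.5% | 45% | 40% |
| 60% | 57% | 54% | 48% |
| 70% | 66.5% | 63% | 56% |

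If the technical-failure objective is met and 5% is read as the share of exercise lost, device failure alone costs at most about 3 points at a true 60%. Anything beyond that would come from non-wear.

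**3. Effect on the barrier analysis.** With equal *m* for everyone, each raw coefficient shrinks by (1 − *m*) and no false barrier arises. With unequal *m*, two groups with the same true adherence *A* differ by *A* × (*m*₂ − *m*₁). Take *A* = 60% and two groups of 60, with *m*₁ = 5%. The chance of P<.05 is about Φ(*d*/SE − 1.96) plus the small opposite tail, with SE = SD × √(2/60). That is 3.65 points at SD 20 and 4.56 points at SD 25.

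| Loss in the two groups | False gap *d* | Chance of P<.05, SD 20 | SD 25 |
|---|---|---|---|
| 5% vs 10% | 3 points | 13% | 10% |
| 5% vs 15% | 6 points | 38% | 26% |
| 5% vs 20% | 9 points | 69% | 51% |

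The SDs and the loss contrasts are all assumed. The two-group comparison is itself a simplification, because the plan would analyse age by linear regression.

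**4. Effect on the recovery analysis.** A simulation with adherence of mean 60% and SD 25 points, and *m* varying between patients, gave:

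| Mean *m* (SD of *m*) | R after loss, from 0.25 | Power (Fisher *z*, from 79%) |
|---|---|---|
| 5% (7 points) | 0.245 | 77% |
| 10% (12 points) | 0.235 | 74% |
| 20% (20 points) | 0.21 | 63% |

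The spread of *m* between patients drives this result. Other assumed spreads gave R from about 0.18 to 0.24 at a mean loss of 10%, and from about 0.15 to 0.23 at 20%.

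**5. Can the planned safeguards correct the value?**
- The software check reports to the researchers, but no section connects a flag to the numerator or denominator.
- The diary comparison can detect systematic under-recording. It covers 2 of up to about 21.7 weeks (5 × 52/12), or about 9%, and only in the strengthening phase. No correction follows from it.
- The survey is collected without a stated role in the calculation.

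**6. What removing the denominator does.** Suppose 100 exercises are prescribed, 60 are done, and a verified device failure covers 10 prescribed exercises, of which 6 were done. As defined, the result is 54/100 = 54%. With the failed period removed from both parts, it is 54/90 = 60%. The shift disappears if the failure is unrelated to adherence.

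**The case against.** **No sentence says that invalid periods are scored zero.** That is true. The article is condensed, and rules for invalid sensor data often sit in an analysis plan that is not shown and may contain one. What stands against this is that the article does more than stay silent. It fixes a numerator and a denominator, and applying them literally gives the downward shift.

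**The safeguards are more than a survey and a diary.** This is also correct. Data are retrieved at clinic visits twice a week, so faults can be found early. Technical failure is targeted below 5%, and the planned agreement analysis against diaries is a direct test for under-recording. The authors declare the limitation openly. These points limit the likely size of device-failure loss and would help reveal non-wear, but they do not alter the value that is analysed.

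**The age link is speculative.** A reader might infer that the barrier analysis will show a false age effect, or that power will fall by a stated amount. The article does not support either inference. It reports no non-wear rate and no difference by age. Its remark on technology skills is offered as a reason for choosing a simple device.

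**Excluding periods on patient report could do harm.** This stands. The section Adherence to Rotator Cuff Rehabilitation itself doubts the validity of self-reported adherence. A patient who skipped exercises could report an unworn watch, and removing those periods would push the rate upward. Voiding a whole 2-week interval for one unworn session would also waste data. Self-report therefore belongs in a sensitivity analysis only.

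**Conclusion.** The point holds as a weakness in the stated measure. Followed as written, participation adherence is biased downward by the factor (1 − *m*), and nothing in the article lets known recording failures change it. At a true 60%, the measured value is 57%, 54% or 48% for an assumed loss of 5%, 10% or 20%.

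A false barrier and a diluted correlation are possible and need further conditions. The first requires loss that differs by predictor; the second requires loss that varies between patients. Their size cannot be fixed from the article, and the figures above shift widely with the assumed SD and spread of loss. The formula also covers recording loss only. Classification error, which the Discussion lists as well, is a separate matter and could move the value either way.

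The stated power calculation is correct on its own terms. The problem is disclosed and partly monitored, so this is a worthwhile and cheap repair and does not invalidate Aim 2.

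**What to change.** In the section that defines participation adherence:

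1. Treat home days or sessions that the verification tool confirms as device failure as missing, and remove the matching prescribed activity from the denominator. Do not drop the whole 2-week interval.
2. In the primary estimate, keep unexplained absence of recording as non-adherence, and label the result a lower bound with respect to recording loss.
3. Add a sensitivity analysis that also excludes periods reported in the survey as exercised without the watch, as the upper bound. It is not a strict bound, because such reports may be wrong in either direction.
4. Report rates of recording failure and of reported non-wear by age and other key predictors.
5. Repeat the adherence-rate, outcome and barrier analyses under both versions.

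**Cost.** One rule and one sensitivity analysis, mostly on data already planned. The article does not give the survey's timing or detail, so it may need to ask for dates of non-wear before step 3 can be done. Some data are lost. Unreported non-wear stays ambiguous, since nothing in the article shows that the software can tell exercise without the watch from no exercise.
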